**Composite secondary outcome: “improved dementia care” through relevant actions**
Medications: donepezil, rivastigmine, galantamine, memantine, donepezil-memantine, antiamyloid monoclonal antibody infusions, and any other Food and Drug Administration–approved medications for dementiaDeprescribing anticholinergic medications: discontinuation or nonrenewal of any of the 41 medications in table 7 (“Drugs with strong anticholinergic properties”) of the American Geriatrics Society Beers Criteria [93]Laboratory tests (cognitive indication only): thyroid-stimulating hormone, vitamin B12, glycated hemoglobin, complete blood count, basic metabolic panel, liver tests, HIV antigen and antibody combination, and syphilis immunoglobulin G and immunoglobulin M antibody with reflexImaging tests (cognitive indication only): computerized tomography (head without contrast) and magnetic resonance imaging (brain without contrast)Specialist referrals for cognitive evaluation: geriatrics, neurology, neuropsychology, psychiatry, geriatric psychiatry, and social workCommunity referrals: Alzheimer’s Association or local support organization

#### Implementation Outcomes

We will begin recruiting implementation study participants after approximately 1 month of patient involvement at each study site, once a “steady state” has been established. We will vary time points for the collection of implementation outcomes throughout our engagement at each clinic in anticipation that informant responses may shift with varied exposure to the 5-Cog. Surveys will assess the implementation outcomes of acceptance, feasibility, and appropriateness, which are considered “leading indicators” of implementation success. These will be measured using the AIM, FIM, and IAM, as noted in the Interventions for the Implementation Study subsection [62,95]. The results of the surveys will be computed using descriptive statistics (central tendency and variability) and, after checking for assumptions (eg, high interclass intraclass correlation), aggregated at the clinic level across all respondents. We will also collect and analyze EMR engagement data (eg, the rates and types of responses to alerts and the use of order sets) to assess the acceptance of EMR tools. In addition, we will collect field notes with observations about the study sites and observations from informal conversations with clinic staff during the study period to better understand the implementation context. Figure 6 summarizes the implementation constructs and the CFIR outcome measurement model for the study.

**Figure 6 figure6:**
[figure not shown]
Consolidated Framework for Implementation Research (CFIR) Measurement Model.

#### Cost-Effectiveness Outcomes

The cost calculator includes parametric models of cost inputs; cost model outcomes from this study will thus allow scenario analyses [67,84]. The proposed calculator will incorporate both the direct costs of the intervention (test administration, staffing costs, etc) and costs associated with interventions prompted by the 5-Cog (brain imaging, specialist referral, laboratory tests, etc). The cost calculator will thus enable others to determine 5-Cog delivery costs and implementation specifics such as the cost of hiring at future implementation sites. Data collected for the BIA will determine financial planning and affordability, while data collected for the CEA will determine the effectiveness and value of the 5-Cog paradigm compared to enhanced usual care.

#### Exploratory Outcomes

Medical billing for cognitive impairment detection paradigms may be an important component of sustainability [22] because PCPs often lack sufficient resources to support the effort required to care for patients with complex needs [96]. The 5-Cog may have benefit in enhancing billing opportunities because it incorporates 5 minutes of cognitive testing and may add to the level of medical complexity of a visit. As noted, one of the 5-Cog 2.0 study interventions—implemented at both 5-Cog and control sites—is provider education on billing for cognitive impairment detection, diagnosis, and treatment. Although the 5-Cog study does not include PCP billing interventions as part of its aims, we will monitor and compare the rates of use of “cognitive” billing codes (eg, Medicare AWV and current procedural terminology codes 96136 and 96138 [97]) between the 5-Cog and enhanced usual care sites. At the 5-Cog sites, we will examine whether the use of “cognitive” billing codes is associated with 5-Cog paradigm administration.

#### Allocation Concealment Mechanism

Randomization is central, computer generated, and not vulnerable to researcher influence. The study statisticians are blinded to interventions and other aspects of the trial.

#### Implementation

The 22 clinic clusters will be phased in gradually for logistical reasons, following a standardized procedure at each clinic: an overview presentation for leadership, a readiness presentation for providers and staff, and then study initiation.

#### Masking

Blinding of patients or PCPs at 5-Cog sites will not be feasible due to the nature of the intervention. However, the outcome is EMR based, and data abstractors will be blinded to allocation. Standardized checklists will be used for outcome measurement to further minimize bias. Statisticians will not be involved in the intervention delivery.

### Data Collection, Management, and Analysis

#### Data Collection Methods

Data will be collected from 2 sources (refer to the following subsections).

##### EMR Data

We will collect EMR data on trial-enrolled patients aged ≥65 years receiving care in the participating practices after obtaining consent from the practice leadership and receiving a waiver from the institutional review board (IRB). Outcomes will be extracted and aggregated from the EMR. Deidentified analytic databases will be created and analyzed by investigators.

##### Feedback From Care Providers, Staff, and Patients

Data on clinician and practice staff perceptions of the intervention and factors that facilitated or impeded implementation and sustainability will be obtained through digital surveys and in-person interviews with key informants. Data on patient perceptions and experiences with the 5-Cog will be obtained through in-person, telephone, and video call platform interviews. Data collection will be the responsibility of the clinical trial staff at the site under the supervision of the site investigators. The investigator will be responsible for ensuring the accuracy, completeness, legibility, and timeliness of the data reported. All source documents will be completed in a neat, legible manner to ensure accurate interpretation of data. Hard copies of the study visit worksheets will be provided for use as source document worksheets for recording data for each participant consented and enrolled in the study. Data recorded in the electronic case report form derived from the source documents will be consistent with the data recorded on the source documents. All effectiveness and implementation data will be entered into REDCap (Research Electronic Data Capture; version 14.0.31; Vanderbilt University), a 21 CFR Part 11–compliant data capture system provided by the Albert Einstein College of Medicine through an NIH grant (UM1TR004400). The data system includes password protection and internal quality checks, such as automatic range checks, to identify data that seem inconsistent, incomplete, or inaccurate.

#### Data Management

Data collected for this study will be analyzed and stored at the Albert Einstein College of Medicine via REDCap. These data will be available through web-based registration to researchers for future analyses after the completion of our pragmatic clinical trial and publication of the main results. For resource-sharing approval, collaborators—both internal and external—will be required to register on the web and submit a resource transfer agreement. Requests can be submitted electronically to expedite research progress. Requests will also be reviewed by the steering committee at regularly scheduled meetings.

#### Effectiveness Study: Statistical Plan

The baseline characteristics of the clinical sites as well as individual enrolled patients will be examined after the baseline measurement time point at the halfway point of target enrollment. It is possible that baseline differences between the groups or missing data will limit the value of data analysis of measurements. Effects on the power to detect differences in the primary outcome will be evaluated and communicated to the principal investigators (PIs), data safety monitoring board (DSMB), and NIH. Given the monitoring plans outlined in the Monitoring subsection, it is exceedingly unlikely that there will be baseline differences between the groups of a magnitude that could threaten the validity of the study.

We will evaluate the clinical effectiveness of the 5-Cog paradigm on new cognitive impairment detection by comparing the proportion of “new MCI and dementia diagnoses” by PCPs within 90 days after the clinic encounter in the 5-Cog paradigm group versus the enhanced usual care group using generalized linear mixed effects (GLME) models with a logit link to account for clinic-clustered data [99]. Using these models, odds ratios of new MCI and dementia diagnoses between the 5-Cog paradigm and enhanced usual care arms will be calculated and tested. We chose a 90-day cutoff because the majority of PCP actions occurred within the first 30 days in our recent RCT [33]. The 22 clinics are cluster randomized to either the 5-Cog paradigm or enhanced usual care arm, which can result in correlated data due to clustering of patients within clinics. This issue will be handled using random effects in the mixed models. Proportions of new MCI and dementia diagnoses for each treatment group will also be reported. We will perform an intention-to-treat analysis. As a secondary approach, we will also perform a per-protocol analysis. All estimates will be reported together with their 95% CIs. The same method will be used for the secondary outcome (“improved dementia care”).

Stratified analyses across the 22 sites will be performed for groups impacted by health disparities, as designated by the NIH, including those from racial and ethnic minority groups (Black and Hispanic individuals) and individuals from socioeconomically disadvantaged backgrounds. Interactions between race and ethnicity and socioeconomic status (SES) will also be explored by stratified analyses by the combination of the 2 factors and by including the 2 factors and their product as well as interactions with the treatment groups in the GLME model for all enrolled patients. We will compare 5-Cog results by location in sensitivity analyses to detect any health care system–based variations.

All sample size and power calculations were performed using 2-tailed tests with a significance level of α=.05. The within-cluster intraclass correlation in this cluster randomized trial is assumed to be 0.05 based on prior studies [100]. On the basis of our RCT data, the proportions of “new MCI and dementia diagnoses” are expected to be 14% and 2% among the 5-Cog and control arms, respectively. The proportions of “improved dementia care” are expected to be 21% and 7% among the 5-Cog and control arms, respectively. In our total sample (N=6600), we have >99% power to detect the overall effectiveness of the 5-Cog paradigm on “new MCI and dementia diagnoses” and the secondary outcome of “improved dementia care.” Sample size determination was based on the primary outcome among individuals from racial and ethnic minority groups (2112/6600, 32%) and those with low SES (3750/6600, 56.82%). Assuming that 80% (1400/1800) of the participants in the 6 Bronx clinics are from racial and ethnic minority groups, and 75% (1350/1800) have low SES, as well as 14% (672/4800) and 50% (2400/4800), respectively, in the 16 Indiana clinics, 300 patients per cluster (clinic) will enable the detection of the effect of the 5-Cog paradigm on new MCI and dementia diagnoses with 81% power among individuals from racial and ethnic minority groups and 99% power among those with low SES.

Our outcomes are ascertained from the EMR by blinded assessors and do not require repeat in-person assessments. This will minimize missing data issues. We will implement robust EMR-based data management processes to further minimize missing data. Cluster sites are not contiguous, and patients within a cluster are assigned to specific PCPs who do not work across sites. Any intentional or unintentional contamination will be monitored by the data team, including by comparing enrolled patient lists across the sites.

#### Implementation Study: Statistical Plan

Interview data will undergo content analysis to identify and score implementation barriers or facilitators. Qualitative content analysis will be performed primarily using a deductive approach, starting from a developed theoretical model—the CFIR—and its associated hypotheses and then examining data to disconfirm or confirm these hypotheses [101]. The analysis will also allow for the inductive development of new themes, categories, and relationships as they arise from the data [102]. Deductive data analysis will be guided by the CFIR constructs and their definitions such that units of qualitative data (sentences or passages) are assigned to ≥1 codes reflecting the CFIR constructs [102]. We will use NVivo 15 (Lumivero) to manage and code qualitative data. For each implementation interview, there will be an artificial intelligence–generated transcript that will be manually reviewed by study staff before it is moved into NVivo. To guide systematic coding, a codebook will be developed. A multiple-analyst team will be trained and tested on its application. Analysts will code a random subset of interviews together during training and then assigned at a ratio of 2 to 3 per transcript for either all or a subset of transcripts, depending on the original level of coding agreement (ie, interrater reliability) [103,104]. Subsequent coding discussions will be held intermittently for the calibration and discussion of difficult cases and disagreements. Interrater reliability will be computed in NVivo at the start, middle, and end of coding, with retraining and adjustments to the plan depending on the results. Inductively, we will allow for the emergence of new codes and subcodes [104]. We will also use applied thematic analysis [105] to identify patterns within and between codes. As much as possible, data analysis will occur in parallel with data collection, enabling us to adjust data collection procedures to capture emerging and unexpected phenomena, as well as perform member checking with informants willing to complete follow-up interviews to review and validate our coding of their initial interviews. Within each CFIR code, for each implementation context or process element, the assigned analyst will add a rating on a scale ranging from +3 (strong facilitator) to −3 (strong barrier) [54]. Analysts will be trained to use evidence from interviews and not personal opinions to rate each driver [102].

RAs in Indiana and the Bronx will be trained by coinvestigators to reliably collect implementation process data from a combination of documents, field notes, and interviews, with select staff responsible for the implementation process. To capture implementation data monthly, while minimizing staff burden, we will use the Prospectively Reported Implementation Update and Score [106]. The analysts will reconstruct these data into process maps or workflow diagrams depicting key historic moments, process variations, and players [54,59,102].

#### Linking Implementation to Effectiveness Analysis

Examining how stakeholder-level factors impact and are impacted by the 5-Cog implementation is critical because implementation can be influenced by stakeholders’ characteristics, attitudes, intentions, and motivations. Stakeholder-level factors are also shaped by organizational factors [107]. Following the guidance of Damschroder and Hagedorn [58], we will link identified and rated (+3 to −3) context and implementation process drivers to implementation outcomes. Our analytical approach is as follows: we will derive clinic-level mean and variability measures of the AIM, FIM, and IAM scales and examine whether these implementation measures are associated with cognitive impairment detection by using GLME models with a logit link, treating the mean and variability measures of the AIM, FIM, or IAM as independent variables [108]. This analysis will determine how detection rates are associated with the levels or variabilities in implementation acceptance, perceived feasibility, and appropriateness within each clinic. We will explore whether and how context variables account for 5-Cog effects on outcomes by including quantitative context measures and interactions with the intervention group as independent variables in the GLME models from the effectiveness analysis [108]. We will then develop a thematic matrix that includes characteristics derived from stakeholder surveys and emerging themes from our qualitative data for each 5-Cog clinic site and conduct side-by-side comparisons—at system, organizational, and staff levels—of the factors that were identified as facilitating or hindering 5-Cog implementation. We will note common and unique factors for each clinic or location. This will generate a list of relevant system-, organizational-, and staff-level factors and processes organized by level of consensus (ie, identified by >1 source) and operational salience (ie, identified as critical for implementation). We will use this list to generate a heuristic model to inform future implementation strategies [54,55].

#### CEA and Economic Impact

Using data from the BIA cost-tracking tool, the cost-effectiveness ratio [109,110] “numerator” will account for site personnel and other costs at both intervention and control sites. The denominator will represent the number of cognitive impairment cases identified at the 5-Cog and control sites. In summary, the cost-effectiveness ratio represents the incremental cost of the 5-Cog intervention compared to enhanced usual care to achieve a clinically meaningful change, divided by the difference in effectiveness, to determine the cost per cognitive impairment case identified. This is expressed as follows:

Cost-effectiveness ratio = intervention costs + Δ (health care costs) / Δ health outcomes (5-Cog) – Δ health outcomes (enhanced usual care comparison group)

To assess uncertainty in our analysis, we will follow the recommendations of the International Society for Pharmacoeconomics and Outcomes Research and the Society for Medical Decision Making Modeling Good Research Practices Task Force [63,65-68,111]. Variability of inputs across study sites with differing levels of social determinants of health will be included in analyses [112]. Differences in intervention and health care costs due to secondary procedures will be assessed individually using negative binomial regression and reported with a 95% CI. Only statistically significant differences from the regression analyses will be incorporated into the cost-effectiveness ratio. Differences in health outcomes will be assessed as described in the Effectiveness Study: Statistical Plan subsection, and the estimate of the GLME model, if significant, will be incorporated into the cost-effectiveness ratio. Costs will be discounted at a 3% annual rate for the trial period, as recommended by the Second Panel on Cost-Effectiveness in Health and Medicine [113].

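### The cost regressions are specified with no stated allowance for clinic, the randomized unit, yet their significance decides which costs enter the cost-effectiveness ratio

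*Protocol article*

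**What the plan says.** The final paragraph of CEA and Economic Impact names the cost method: arm differences in the cost of the intervention and of the care that it prompts "will be assessed individually using negative binomial regression and reported with a 95% CI". It then sets a selection rule: "Only statistically significant differences from the regression analyses will be incorporated into the cost-effectiveness ratio". The next sentence treats effects differently: "Differences in health outcomes will be assessed as described in the Effectiveness Study: Statistical Plan subsection", so the effect estimate comes from the generalized linear mixed effects (GLME) model. Earlier in the same paragraph it adds: "Variability of inputs across study sites with differing levels of social determinants of health will be included in analyses".

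Under Effectiveness Study: Statistical Plan, the article explains that clinics were the units randomized, "which can result in correlated data due to clustering of patients within clinics", and that "This issue will be handled using random effects in the mixed models". That statement concerns the diagnosis models and, by extension, the secondary outcome. For power, "The within-cluster intraclass correlation in this cluster randomized trial is assumed to be 0.05 based on prior studies". No ICC, interval width or power is given for costs.

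**The concern.** The article names the cost estimator, its output and the decision that hangs on it. It says how clinic correlation is handled for the effectiveness outcomes and sends health outcomes back to that section, but makes no such link for costs. An analyst who follows the cost sentence literally fits an ordinary negative binomial regression to patients from 22 randomized clinics.

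In most analyses a standard error that is too small only makes the interval too short. Here significance is the entry condition for the ratio, so it can also change which cost items are counted and hence the point estimate for the third aim.

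A separate problem lies in the named model. Negative binomial regression describes counts. Costs are skewed amounts, many of them probably zero, and the model's variance function is not neutral to the unit of money.

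**Working it through.** **The plan's own figure.** Inputs from Planned Sample Size, Sequence Generation and the Statistical Plan: 22 clinics, about 300 patients each, 1:1 allocation (3300 patients per arm), ICC 0.05, expected diagnosis rates 14% and 2%, two-sided 5% level.

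- Design effect: DE = 1 + (300 − 1) × 0.05 = 15.95.
- Effective size per arm: 3300 / 15.95 = 206.9.
- Null SE = √(2 × 0.08 × 0.92 / 206.9) = 0.0267. Alternative SE = √((0.14 × 0.86 + 0.02 × 0.98) / 206.9) = 0.0260.
- Power = Φ((0.12 − 1.96 × 0.0267) / 0.0260) = Φ(2.60) = 99.5%.

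This agrees with the stated power above 99% for the primary outcome. The plan's sizing therefore fits a design effect of about 16.

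**If clinic is left out of the cost model.** The true SE is √DE times the reported one, and the real type I error is 2 × (1 − Φ(1.96 / √DE)). The cost ICC is an assumption, so a range is shown.

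| Assumed cost ICC | DE | SE understated by | Type I error |
|---|---|---|---|
| 0.001 | 1.299 | 1.14 | 8.5% |
| 0.005 | 2.495 | 1.58 | 21% |
| 0.01 | 3.99 | 2.00 | 33% |
| 0.02 | 6.98 | 2.64 | 46% |
| 0.05 | 15.95 | 3.99 | 62% |

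**Check by simulation.** Unclustered negative binomial fits to 22 clinics of 300, no arm effect, with an assumed mean of 500 and dispersion of 1.5, over 300 runs. With no clustering, 7% of runs rejected. At ICC 0.01 the reported SE was 0.0302 against an actual 0.0585 (1.9-fold, 28% rejected). At ICC 0.05 it was 0.0302 against 0.1185 (3.9-fold, 62% rejected). A second simulation gave 31% and 67%.

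**Currency unit.** With arm means μ and dispersion α, the model's variance for the log cost ratio is the sum over arms of (1/μ + α)/n. Changing the unit changes both 1/μ and the fitted α. In one simulated dataset (assumed: 3300 per arm, 60% zeros, the rest lognormal with log mean 6 and log SD 1, no clustering, α estimated by maximum likelihood), the arm coefficient was the same in every unit, but its SE was 0.115 in cents, 0.092 in dollars and 0.051 in thousands of dollars.

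The correct SE follows from the assumed distribution. The squared coefficient of variation is 0.4e¹⁴ / (0.4e^6.5)² − 1 = 2.5e − 1 = 5.80, so the SE is √(2 × 5.80 / 3300) = 0.059. The unit alone moves the interval from too wide to too narrow.

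The table therefore assumes that the regression gets the within-clinic variance right. In this example the dollar-scale SE is too large by 0.092 / 0.059 = 1.56. That would about cancel the clustering error at ICC 0.005 and leave a shortfall of 3.99 / 1.56 = 2.6-fold at ICC 0.05. Such cancelling is accidental and cannot be relied on.

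**The case against.** A reader might infer that the plan ignores clustering for costs and that its intervals are certain to be far too narrow. The documents do not support that.

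- The text is silent on clustering and excludes no adjustment. A negative binomial model can carry a clinic random effect or cluster-robust errors. Assessing differences individually means one at a time; it does not mean that patients are treated as independent. An article may leave such detail to the full protocol or a health-economic plan, and the team plainly knows that the design is clustered.
- The ICC of 0.05 belongs to the power calculation. That costs cluster as strongly as diagnoses is not shown, and at 0.001 the harm is mild.
- Price and record-system differences between the Bronx and Indiana add little to the error of the arm contrast, because allocation is 1:1 within each site. Only variation between clinics within a health system counts.
- At a fixed dispersion the count term is trivial in dollars: with mean 500 and dispersion 1.5 it is 500 of 500 + 1.5 × 500² = 375,500, or 0.13%. The model then nearly has a gamma variance, and unlike a gamma likelihood it accepts zeros.

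The first three points stand and limit the claim. They do not remove it: the estimator and the selection rule are both fixed in print, and costs are left without the link to the clustered model that health outcomes receive. The sentence on variability of inputs across sites does not adjust a standard error. The fourth point holds only while the dispersion is fixed. Once it is estimated from zero-heavy data, the unit matters, as the example shows.

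**Conclusion.** The point holds in conditional form. The cost regressions are named with no stated allowance for the randomized unit, and if run as written their intervals would be too narrow. The size depends on a cost ICC that the article does not give. Over the assumed range of 0.001 to 0.05 the SE is understated 1.1- to 4.0-fold and the type I error is about 9% to 62%, given 300 patients per clinic and a correct within-clinic variance. Even at 0.005 the false-positive rate is about four times nominal. Because significance admits a cost to the ratio, the error reaches the economic result itself. The unsuitability of a count model for dollar amounts stands apart from clustering. None of this touches the primary effectiveness analysis, which does account for clinic.

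**What to change.** State in the cost-effectiveness section that:

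1. Cost differences are estimated with a model that accounts for clinic, by a clinic random intercept or by cluster-robust errors with a small-sample correction for 22 clusters, and that includes site (Bronx or Indiana) as a fixed effect.
2. The cost model suits skewed amounts with zeros: a two-part model or a quasi-likelihood log-link model. Negative binomial regression is kept for counts of services. A plain gamma likelihood will not do, because it is undefined at zero.
3. Estimated cost differences enter the ratio with their clustered intervals whether or not they are significant. Without this, the wider intervals from item 1 would drop more cost items under the present rule.

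A clinic bootstrap stratified by arm and site is not a safe substitute. Six Bronx clinics split 1:1 leave about three per arm, and resampling three clusters understates between-clinic variance by about a third ((3 − 1)/3 = 2/3).

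The cost is wording and wider intervals; the data are the same. The article reports enrollment still under way in December 2024 (2369 of 6600 patients). The change should be fixed before costs are compared by arm.

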**Methods:**

We will enroll 6600 older patients with cognitive concerns from 22 primary care clinics in the Bronx, New York, and in multiple locations in Indiana for this hybrid type 1 effectiveness-implementation trial. We will analyze the effectiveness of the 5-Cog paradigm to increase the rate of new diagnoses of mild cognitive impairment syndrome or dementia using a pragmatic, cluster randomized clinical trial design. The secondary outcome is the ordering of new tests, treatments, and referrals for cognitive indications within 90 days after the study visit. The 5-Cog’s decision support component will be deployed as an electronic medical record feature. We will analyze the 5-Cog’s implementation process, context, and outcomes through the Consolidated Framework for Implementation Research using a mixed methods design (surveys and interviews). The study will also examine cost-effectiveness from societal and payer (Medicare) perspectives by estimating the cost per additional dementia diagnosis.

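### Cost and effect differences enter the cost-effectiveness ratio only if significant, which biases the incremental cost, and the scale of the effect is not reconciled with a count of cases

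*Protocol article*

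**What the plan says.** All of the following is from the Protocol article.

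- **Costs.** Under CEA and Economic Impact, differences in intervention costs and in follow-on health care costs "will be assessed individually using negative binomial regression and reported with a 95% CI". The next sentence is the rule at issue: "Only statistically significant differences from the regression analyses will be incorporated into the cost-effectiveness ratio".
- **Effect.** The same paragraph says that "the estimate of the GLME model, if significant, will be incorporated into the cost-effectiveness ratio". Effectiveness Study: Statistical Plan specifies "generalized linear mixed effects (GLME) models with a logit link to account for clinic-clustered data" and says that "odds ratios of new MCI and dementia diagnoses between the 5-Cog paradigm and enhanced usual care arms will be calculated and tested". It adds: "Proportions of new MCI and dementia diagnoses for each treatment group will also be reported".
- **Target.** CEA and Economic Impact describes the denominator as a count of impaired patients found, and the purpose of the ratio as "to determine the cost per cognitive impairment case identified". The Methods paragraph of the Abstract instead promises "estimating the cost per additional dementia diagnosis".

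**The concern.** An incremental cost-effectiveness ratio is an estimate: the difference in mean cost divided by the difference in mean effect. Failing to reach P<.05 does not show that a difference is zero, yet the rule treats it so. An item that does reach P<.05 has been selected for being large in this sample, so it is kept at a value too large on average. The two errors do not cancel; the expected total is pulled toward zero. Testing item by item makes this worse, because several moderate differences can each fail while their sum is clearly real.

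Aim 3 would then depend on which cost items happen to cross a threshold. The rule also sits badly with Cost-Effectiveness Outcomes, where the calculator is to include both delivery costs and the costs of tests and referrals that the 5-Cog prompts. And an item dropped from the ratio brings no sampling error into it, although the same paragraph commits to recognised guidance on uncertainty.

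The second issue is scale. An odds ratio from a logit model is not a number of additional cases, and the article does not say how one becomes the other.

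**Working it through.** **Inputs from the article.** Two-sided α=.05, intraclass correlation 0.05, planned proportions 14% v 2% (Effectiveness Study: Statistical Plan); about 300 patients in each of 22 clinics, 6 in the Bronx and 16 in Indiana (Planned Sample Size); 1:1 allocation within site (Sequence Generation). That gives 3300 patients and 11 clinics per arm. No cost means, variances or cost intraclass correlations are given, so everything on costs below is for assumed power.

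**1. The plan's own power figure, which governs the gate on the effect.**
- Design effect: 1 + (300 − 1) × 0.05 = 15.95.
- Effective number per arm: 3300 / 15.95 = 206.9.
- SE under the alternative: √[(0.14×0.86 + 0.02×0.98) / 206.9] = 0.0260.
- SE under the null, pooled proportion 0.08: √[2×0.08×0.92 / 206.9] = 0.0267.
- Power: Φ[(0.12 − 1.96×0.0267) / 0.0260] = Φ(2.60) = 99.5%. With a t distribution on 20 degrees of freedom it is 99.0%.

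The stated figure of more than 99% is reproduced to within this approximation. Under the planning assumptions, the gate on the effect would leave no denominator in about 0.5–1% of trials.

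**2. The filter on one cost item.** Let the estimate in SE units be X ~ N(μ, 1), set to 0 unless significant. Ignoring the negligible opposite tail, power = Φ(μ − 1.96) and the expected filtered value is μ × power + φ(1.96 − μ).

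| Assumed power | μ | Expected filtered value | As share of truth | Overstatement if kept |
|---|---|---|---|---|
| 30% | 1.436 | 1.436×0.30 + 0.348 = 0.778 | 54% | 0.54/0.30 = 1.8 |
| 50% | 1.960 | 1.960×0.50 + 0.399 = 1.379 | 70% | 0.70/0.50 = 1.41 |
| 80% | 2.802 | 2.802×0.80 + 0.280 = 2.521 | 90% | 0.90/0.80 = 1.12 |

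**3. Several items filtered one by one.** Assume six independent items, each with a true difference of 1.5 SE (power 32% each).
- The unfiltered total is 6×1.5 / √6 = 3.67 SE, so it would be significant with power Φ(3.67 − 1.96) = 96%.
- The filtered sum averages 56% of the truth.
- It is exactly zero with probability (1 − 0.323)⁶ = 0.677⁶ ≈ 0.096, about 1 trial in 10.

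**4. Scale of the effect.** At 14% v 2%:
- risk difference 0.14 − 0.02 = 0.12, or 0.12 × 3300 = 396 extra cases per arm of 3300;
- odds ratio (0.14/0.86) / (0.02/0.98) = 7.98, log odds ratio 2.08.

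For an assumed incremental cost of $100 per patient (range $50–$200), cost per additional case is 100/0.12 = $833 ($417–$1,667). Dividing by the odds ratio would give $12.5, too small by a factor of 7.98/0.12 ≈ 66; dividing by the log odds ratio would give $48, too small by about 17. Nor can the odds ratio alone be turned into cases: 7.98 implies a risk difference of 0.065 at a 1% control rate and 0.37 at 10%.

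**The case against.** Several stronger readings are tempting, and the article does not support them.

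- **The ratio will be undefined.** A reader might infer this from the condition on the effect. No fallback is stated, but under the planning assumptions the condition fails in only about 0.5–1% of trials.
- **The plan divides by an odds ratio.** It does not say so. It says that the model estimate is incorporated, describes the denominator as a number of cases, and reports proportions by arm. The conversion may well be set out in the full plan. What stands is that the article names a logit-model estimate as the input and a count as the result, and leaves the two unreconciled.
- **The 5-Cog will look cheaper than it is.** This holds only if the dropped items are added costs. Cost-Effectiveness Assessment allows that follow-up costs may be offset by savings, and dropping savings makes the 5-Cog look dearer.
- **The printed formula is wrong because it lacks brackets.** The sentence before it gives the structure, so this is typesetting.

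It is also fair to say that prompted orders may not be badly underpowered. The composite secondary outcome is expected at 21% v 7%, which by the same approximation has about 98–99% power. Single components would have less, however, and costs vary more than the presence of an order. Finally, each cost difference is reported with a 95% CI and scenario analyses are planned, so uncertainty is not hidden altogether. But none of this removes the significance rule, which is explicit and is not cancelled elsewhere in the article.

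**Conclusion.** The significance conditions are wrong as written. For a cost item with 30% to 80% power, the rule delivers on average 54% to 90% of the true difference and overstates the items that pass by 1.8- to 1.12-fold. These sizes rest on assumed power and approximately normal estimates; the six-item example also assumes independence. The direction of the error in the final ratio cannot be stated in advance.

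The condition on the effect is the same error in principle, but would rarely bite at the planned rates. The effect scale is an inconsistency to be reconciled. The unit of effect in the Abstract (dementia only) differs from that in CEA and Economic Impact (cognitive impairment) and from the primary outcome (MCI or dementia), which is a minor wording matter.

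Severity: should be fixed. Only aim 3 is affected; the primary test, the sample size and the data collection are not.

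**What to change.** 1. Delete both significance conditions. Use the point estimates of all incremental costs and of the effect, whatever their P values.
2. State that the effect is the marginal difference in the proportion newly diagnosed with MCI or dementia, derived from the mixed model by averaging predicted probabilities under each arm.
3. Show the joint uncertainty of cost and effect with a method that respects clustering and the small number of clinics, such as a bivariate mixed model or a clinic-level bootstrap with a small-sample correction. A plain bootstrap stratified by arm and site would resample about 3 Bronx clinics per arm, and its variance in that stratum would be too small by a factor of (3 − 1)/3, that is, by about one third.
4. Use the MCI-or-dementia unit in the Abstract as well as in Methods.

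The cost is some wording and a little programming, with no new data. The interval around the ratio will be wider. Enrolment was still under way in December 2024 according to the Results section, so the rule should be changed before comparative cost results are seen.
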